#### Instruments

The survey questionnaire includes questions about primary outcomes: household economy (income-generation, income, assets, housing, relative household status, health insurance), child nutritional status; and unmet need of family planning. Secondary outcome variables encompass gender norms and rights (perception of women’s rights and gender equity, women’s participation in decision-making and income-generation, women’s utilization of reproductive health services, and women’s perceived self-efficacy to speak out in community meetings). Further questions include information about the household structure (household composition and headship),, and individual socio-demographic information (age, education, marital status, number of children), and program-related variables (participant of VSLA, time in VSLA, partner participation in men’s reflection groups) (Table 2). A locally adapted composite wealth score is calculated based on structure of the house, type of fuel for cooking, toilet facility, food security, and having a mobile phone or TV. Questions from previously validated instruments are used if available (Demographic and Health Survey [7], Food-insecurity experience scale [50], Gender-equitable Men scale [51]). Anthropometric data is collected from children under 5 years of age living in the household including weight, height and mid-upper arm circumference (MUAC). An overview over the indicators used is provided in Table 2.

**Table 2 Tab2:** Study variables

Variables	Type of variable	Units
1. Primary outcomes		
Household economy		
Assets	Categorical	
Relative household economic status	Categorical	
Household food security	Likert scale, Qualitative data	1–3
Income-generating activities	Categorical	
Income	continuous	
Housing	categorical	
Composite wealth indicator, asset based	Categorical	
Child nutritional status		
Weight	Continuous	Kg
Height	Continuous	Cm
MUAC	Continuous	Mm
Weight for Height	categorical	
Weight for age	Categorical	
Height for age	categorical	
Unmet need of family planning		
Counselling and use of FP	Binary	Yes or no
2. Secondary outcomes		
perception of women’s rights and gender equity,, and	Likert scale, Qualitative data	
women’s participation in decision-making and income-generation,	Likert scale, Qualitative data	
women’s utilization of reproductive health services		
Attendance of ANC during last pregnancy	Binary Qualitative data	Yes or no
Place of delivery of the last child	Categorical	Hospital, health care facilities, home
women’s perceived self-efficacy to speak out in community meetings	Likert scale, Qualitative data	
3. General characteristics		
Sex	Binary	Male/female
Age	Continuous	Months
Marital status of parents/tutor	Categorical	Married, single, divorced,
Household size	Continuous	
Sex of main breadwinner	Binary	Male/female
4. Program-related variables		
Belonging to VSLA	Binary	Yes or no
Time in VSLA	Continuous	
Partner or husband engaged in peer-to-peer reflexion group	Binary	Yes or no

#### Sample size calculation/justification

The power calculation is based on the hypothesis that establishing savings and loan systems at the village level lowers the risk of stunting of children up to the follow-up. Improved child growth is a result of increased livelihood and food security that is sustainable over some time. The surveys are conducted in 80 villages with an average of 15 households per village (1200 households). Assuming an attrition rate of 30% during follow-up this results in a final analytic sample size of 800. The control group is planned to be smaller with 40 villages (600 households). Assuming the same attrition rate there must be 400 households recruited to participate in the final control arm.

As there are few data on the distribution of individual growth rates among children in the study area, we express the intervention effect in terms of a certain fraction of the standard deviation SD of individual growth rates. If the mean change in height during a given time period increases by z standard deviations as a consequence of the intervention, then this corresponds to a shift of the median of growth to the Φ (z)-quantile of the distribution in the control group (where Φ denotes the cumulative density function of the standard normal distribution. For instance, if z = 0.25, this corresponds to an intervention-related shift of the distribution whose new median is where the 60th percentile of the original distribution was.

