#### Statistical analysis plan

An intention-to-treat analysis comparing all persons who were initially participating in a VSLA with a control group will establish the effect of participating in the project on household economies (composite wealth score; number of income-generating activities), on child nutritional status (height for age z-score HAZ, weight for age z-score WAZ, and weight for height z-score WHZ, mid-upper-arm circumference), and on the use of family planning (current use of modern family planning method; unmet need for contraception) as the primary outcomes.

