##### Secondary outcomes

In addition to the primary outcomes, secondary outcomes include changing gender norms (attitudes towards women’s rights, gender-based violence, women’s roles) and women’s empowerment (participation in the economy; self-efficacy to express their views; intra-household decision-making; use of health services; gender-based violence). (Table 3).

**Table 3 Tab3:** Power calculations for child anthropometric data

Effect size	Shift of median to	ICC^a^	SD of random village effect	Child in every HH	Child in 50% HH
				Power	Power
0.27 SD	P61	0.01	0.1 SD	99%	86%
		0.02	0.14 SD	98%	84%
		0.03	0.18 SD	97%	83%
		0.04	0.21 SD	96%	81%
		0.05	0.23 SD	95%	79%
		0.10	0.33 SD	86%	–
0.25 SD	P60	0.01	0.1 SD	97%	80%
		0.02	0.14 SD	96%	78%
		0.03	0.18 SD	95%	77%
		0.04	0.21 SD	93%	75%
		0.05	0.23 SD	91%	73%
		0.10	0.33 SD	80%	–
0.2 SD	P58	0.01	0.1 SD	88%	–
		0.02	0.14 SD	84%	–
		0.03	0.18 SD	81%	–
		0.04	0.21 SD	78%	–
		0.05	0.23 SD	75%	–

Table 3 gives the achievable power for different effect sizes and intra class correlation coefficients. The expected power is given both under the assumption that a) a child under 5 years old will be found in each household, and b) that a child under 5 years old is found only in every other household. Intra-class coefficients reported in other African contexts range from 0.01 to 0.05

*SD* standard deviation of individual growth rates

^a^Proportion of variance explained by the factor village

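### The power calculation names stunting risk as its hypothesis, but Table 3 gives power only for a difference in mean growth, and that power does not carry over to stunting

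*Protocol article*

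**What the plan says.** Under Sample size calculation/justification, the protocol article opens with its hypothesis: "The power calculation is based on the hypothesis that establishing savings and loan systems at the village level lowers the risk of stunting". The Primary outcomes section defines stunted as HAZ below -2 SD, with moderate and severe grades below that line, so a risk of stunting is a proportion.

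The next paragraph of the sample size section changes scale: "we express the intervention effect in terms of a certain fraction of the standard deviation SD of individual growth rates". Its worked example is a mean shift: "For instance, if z = 0.25, this corresponds to an intervention-related shift of the distribution". The footnote to Table 3 gives the unit of every effect size in the table as the "standard deviation of individual growth rates". No control-group stunting prevalence, stunting difference or power for stunting is given.

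The type of the height endpoint also varies. The Statistical analysis plan section lists the effect "on child nutritional status (height for age z-score HAZ" among the primary outcomes, as a z-score. Table 2 lists height as continuous and height for age as categorical.

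**The concern.** The named hypothesis and the calculated quantity are different endpoints. A shift of a quarter of an SD in one year's growth is a smaller shift on the scale of attained HAZ whenever growth varies less between children than HAZ does, and cutting HAZ at -2 SD then discards further information. Power worked out for mean growth therefore cannot be read as power for stunting.

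Table 3 supplies the only power figures in the article. A reader who takes the opening sentence at its word would credit the study with over 90% power for stunting in the more favourable column, and could read a null stunting result as good evidence of no effect. The plan has not established that.

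**Working it through.** **Step 1: reproduce Table 3.** Inputs from the sample size section: 80 intervention and 40 control villages, with 800 and 400 households analysed, so 10 per village (5 if only every other household has a child). ICCs are those of Table 3. Significance level and sidedness are not stated; two-sided 0.05 is assumed.

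- Design effect: DE = 1 + (m - 1) × ICC, with m = 10 or 5.
- Effective control n = 40m / DE; intervention n is twice that.
- The SD is taken as the within-village SD, so total SD = 1/√(1 - ICC). This matches the village-effect column of Table 3: √(0.05/0.95) = 0.23.
- Power = Φ(effect / SE - 1.96).

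For 0.25 SD, m = 10:

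- ICC 0.01: DE = 1.09; n = 367 and 734; SE = 1.005 × √(1/367 + 1/734) = 0.0643; power = Φ(3.89 - 1.96) = 97.3%.
- ICC 0.05: DE = 1.45; n = 276 and 552; SE = 1.026 × √(1/276 + 1/552) = 0.0757; power = Φ(3.30 - 1.96) = 91.1%.

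Table 3 prints 97% and 91%. All 27 printed cells reproduce within 1 point. The table is therefore a continuous-growth calculation, and a correct one.

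**Step 2: carry the same effect to stunting.** Two inputs are not in the article and are assumed:

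- Control stunting prevalence p0 = 43%. The Background gives this figure for malnourished children under five nationally; it is a proxy.
- ρ = SD of 12-month growth / SD of HAZ, from 0.3 to 1.0.

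A growth effect of 0.25 SD shifts mean HAZ by 0.25ρ HAZ SDs, so the intervention prevalence is p1 = Φ(Φ⁻¹(0.43) - 0.25ρ). The two proportions are compared with the pooled-variance formula and the effective n from Step 1.

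Example, ρ = 0.5, ICC 0.01: p1 = Φ(-0.176 - 0.125) = 38.2%, a difference of 4.84 points. The null and alternative SEs are 0.0313 and 0.0315. Power = Φ((0.0484 - 1.96 × 0.0313)/0.0315) = 34%.

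Power at ICC 0.01 / 0.05, a child in every household (Table 3 for growth: 97% / 91%):

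| ρ | Stunting, control to intervention | Endline comparison | Change in stunting from baseline |
|---|---|---|---|
| 1.0 | 43% to 33.5% | 87% / 76% | 74% / 62% |
| 0.7 | 43% to 36.3% | 58% / 47% | 61% / 49% |
| 0.5 | 43% to 38.2% | 34% / 27% | 48% / 38% |
| 0.3 | 43% to 40.1% | 15% / 13% | 32% / 25% |

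An unpooled variance lowers the endline figures by up to about 1 point. The change column takes baseline and endline HAZ as bivariate normal with correlation 1 - ρ²/2.

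With a child in every other household (Table 3: 80% / 73%), endline power runs from 61% / 55% at ρ = 1.0 to 10% / 9% at ρ = 0.3, and change-from-baseline power from 47% / 42% to 19% / 17%.

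**Step 3: sensitivity (a child in every household).**

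- Prevalence 20%: endline power 75% / 64% at ρ = 1.0 and 28% / 22% at ρ = 0.5.
- Prevalence 60%: 87% / 77% and 34% / 27%.
- A smaller ICC for the binary outcome (0.0063 and 0.0315, derived from the continuous ICCs): 87% / 79% at ρ = 1.0.
- A simulated village-level test adjusted for baseline stunting, with HAZ SD 1.2-1.4 and ICC 0.01-0.05: about 33-40% at a change SD of 0.4 (ρ = 0.29-0.33), 52-63% at 0.7 (ρ = 0.50-0.58) and 69-83% at 1.0 (ρ = 0.71-0.83).

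**The case against.** The article moves openly from the stunting sentence to growth, says that it works in SDs of growth, and labels Table 3 that way. It nowhere prints 91-97% as power for stunting prevalence. Its abbreviation list glosses HAZ with the word stunting, so the opening sentence may be loose shorthand for poor linear growth. Continuous height and HAZ are listed primary outcomes, and mixed models of change from baseline to endline are planned. Table 3 thus serves an analysis close to one already in the plan. All of this stands, and it is why the remedy is small. It does not remove the contradiction: the sentence speaks of a risk, and the Primary outcomes section defines stunting by a cut-off.

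Two stronger readings are not supported.

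- A reader might infer that power for stunting is mostly below one half. That depends on the unstated SD ratio and prevalence and on the analysis chosen. The endline comparison exceeds one half at a ratio of 1.0, and the baseline-adjusted test does so once the ratio reaches about 0.5.
- A reader might infer that children aged 4-5 at baseline drop out of the growth cohort, because recruitment covers ages 1-5 while the Instruments section says "Anthropometric data is collected from children under 5 years of age living in the household". Nothing in the article reapplies an age limit at follow-up, and both statements read naturally as age ranges at enrolment. No loss of power should be claimed on that ground.

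**Conclusion.** The mismatch is real and visible in the article's own text: the hypothesis named for the power calculation is binary, and the quantity powered is continuous. Table 3 is not miscalculated, but its figures do not apply to stunting.

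The direction is firm, since power for stunting was below the matching Table 3 value in every scenario tried. The size is not. With 43% prevalence and a child in every household, endline power ranges from about 75-87% at a ratio of 1.0, the most favourable tried, down to 12-15% at 0.3. Analysed as change from baseline it is about 25-74% over the same ratios, and a baseline-adjusted test may do better. These ranges rest on an assumed prevalence, an assumed SD ratio, normally distributed HAZ and a two-sided 5% level. None of this shows that the sample is too small for the continuous growth comparison.

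**What to change.** - In the sample size section, replace the stunting-risk hypothesis with a between-arm difference in mean 12-month growth, naming the measure (change in height or change in HAZ) and stating that it is continuous.
- Label Table 3 as power for that difference, and state the significance level and sidedness.
- Either say that Table 3 does not give power for stunting prevalence, or add that power as a range with the assumed prevalence, SD ratio and analysis.
- Reconcile Table 2, where height for age is categorical, with the HAZ z-score in the Statistical analysis plan section, and say which form is the primary analysis.

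The cost is a few sentences and a table note. No extra data or participants are needed. If power for stunting is printed, it will look less favourable than Table 3.

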#### Data collection

A team of local researchers fluent in the locally spoken languages is trained over a week in data collection methods, followed by a pilot study. Participation in the survey is voluntary and refusal to participate will have no repercussion whatsoever. The study information and consent forms are translated into local languages. Informed verbal and written consent is obtained from each individual prior to the beginning of data collection. Data will be collected strictly respecting confidentiality. No compensation will be offered in exchange for participation in the survey and no fees will be required from participants. The structured questionnaire is administrated using tablet technology and the Open Data Kit (ODK) software package. Data is stored on a secured server located at the Swiss Tropical and Public Health institute in Basel.

Anthropometric measurements of children are taken by trained surveyors using a weighing scale, a tape measure and a (Mid-upper arm circumference) MUAC measuring tape [52].

#### Statistical analysis plan

An intention-to-treat analysis comparing all persons who were initially participating in a VSLA with a control group will establish the effect of participating in the project on household economies (composite wealth score; number of income-generating activities), on child nutritional status (height for age z-score HAZ, weight for age z-score WAZ, and weight for height z-score WHZ, mid-upper-arm circumference), and on the use of family planning (current use of modern family planning method; unmet need for contraception) as the primary outcomes.

##### Primary outcomes

Household economic status will be assessed using an asset-based wealth score and number of income-generating activities. For the analysis and validation of scaling properties of the composite wealth score principal component analysis will be used.

To measure child nutritional status, measures of chronic and acute malnutrition will be used. Stunting (small-for-age) as measure of chronic malnutrition will be measured as height for age index z-scores (HAZ): a HAZ < − 2SD was defined as stunted, a HAZ between -2SD and − 3 SD was defined as moderate stunting and a HAZ < − 3 z-score was defined as severe stunting. Underweight will be measured as weight for age index z-scores (WAZ): a WAZ < − 2SD was defined as underweight, a WAZ between – 2SD and − 3 SD was defined as moderate underweight and a WAZ < − 3SD was defined as severe underweight. Wasting, measuring acute malnutrition as weight for height z-scores (WHZ) < − 2 SD, a WHZ between – 2SD and – 3SD as moderate wasting and a WHZ < −3SD as severe wasting. A MUAC < 115 mm will also define a severe malnutrition [52–54]. To measure food security, the FAO food insecurity experience scale is used [50]. Family planning use is measured as proportion of women currently using modern contraceptives, and as unmet need for family planning.

##### Secondary outcomes

In addition to the primary outcomes, secondary outcomes include changing gender norms (attitudes towards women’s rights, gender-based violence, women’s roles) and women’s empowerment (participation in the economy; self-efficacy to express their views; intra-household decision-making; use of health services; gender-based violence). (Table 3).

**Table 3 Tab3:** Power calculations for child anthropometric data

Effect size	Shift of median to	ICC^a^	SD of random village effect	Child in every HH	Child in 50% HH
				Power	Power
0.27 SD	P61	0.01	0.1 SD	99%	86%
		0.02	0.14 SD	98%	84%
		0.03	0.18 SD	97%	83%
		0.04	0.21 SD	96%	81%
		0.05	0.23 SD	95%	79%
		0.10	0.33 SD	86%	–
0.25 SD	P60	0.01	0.1 SD	97%	80%
		0.02	0.14 SD	96%	78%
		0.03	0.18 SD	95%	77%
		0.04	0.21 SD	93%	75%
		0.05	0.23 SD	91%	73%
		0.10	0.33 SD	80%	–
0.2 SD	P58	0.01	0.1 SD	88%	–
		0.02	0.14 SD	84%	–
		0.03	0.18 SD	81%	–
		0.04	0.21 SD	78%	–
		0.05	0.23 SD	75%	–

Table 3 gives the achievable power for different effect sizes and intra class correlation coefficients. The expected power is given both under the assumption that a) a child under 5 years old will be found in each household, and b) that a child under 5 years old is found only in every other household. Intra-class coefficients reported in other African contexts range from 0.01 to 0.05

*SD* standard deviation of individual growth rates

^a^Proportion of variance explained by the factor village

First, descriptive statistics will be calculated for the primary and secondary outcome variables, and for socio-economic characteristics. Assets, number of income-generating strategies, food security and child nutritional status, use of family planning and other reproductive health services, and related knowledge, and prevalence of perceptions of gender relations (beliefs and attitudes), and prevalence of different levels of knowledge on sexual and reproductive health including use of family planning methods and existing services will be documented. For this purpose, percentages, means and standard deviations will be computed. To assess self-efficacy and decision-making power, indices will be built using Mokken analysis, which is a nonparametric procedure based on item-response theory that has been used to assess similar scales in previous studies [55, 56]. Differences between education level, rural and urban populations will be assessed statistically using Chi2 tests for different degrees of freedom for categorical variables, or using t-tests for continuous variables.

To assess the program effects, mixed-effect regression models will be run for each primary outcome variable to establish change in the outcome variables over time (baseline to endline) and by intervention and control group. The models will be adjusted for socio-economic confounders, and clustering will be considered at the level of villages. The same analysis as for primary outcomes will be conducted for secondary outcomes. In addition, the role of mediating factors will be investigated. It will be explored whether a change in the power of decision-making mediates changes in household economic status and use of family planning (FP). In addition, we will study whether children’s nutritional status improves if men are supportive of women’s economic activities. For this purpose structural equation modelling (SEM) with maximum likelihood estimation will be conducted to investigate the complex and multidimensional pathways by which the association of a positive masculinity and women’s empowerment directly or indirectly affect household economics status, children nutritional’s status and use of reproductive health services, and the potential role of mediating variables.

Results will be discussed under consideration of the fidelity of the intervention. Women who complete the full cycle of a VSLA and men who participate in the full cursus of the peer-to-peer sensitisation group will determine the level of fidelity.

Analysis will be conducted with STATA V.15.

### Study 2 - qualitative component

A qualitative study with households participating in a VSLA will be conducted, collecting data on gender relations, women’s economic participation and access to sexual and reproductive health services.

#### Study design

Qualitative studies are by nature smaller and capable of providing in-depth insights into processes within selected households and couples of a particular study site [57].

With the qualitative study, women and their partners are closely followed through multiple interviews, including collection of information related to their income and expenditure, as well as information on gender-based dynamics within families and communities. Health-related behaviour and perceptions of family planning will also be explored in the context of men engaged and women’s empowerment to assess a change in behaviours and perceptions after men’s sensitization as well motivations for the change.

#### Instruments

For the qualitative interviews a guide is developed focusing on the impact participation in the project has on women’s families in terms of gender-relations, household economy, and health. Over time, the instrument is adapted based on the results from previous interviews to capture emerging themes. Focus group discussions (FGD) with 6–8 participants, with women and men separately will be organized as well as individual in-depth interviews (IDIs). We will use purposive sampling to recruit 18–49 years old women participating in VSLA whose husbands are also participating in either VSLA or a reflection group. Two focus groups will be organized with the same participants after a one-year interval. We plan to do five to seven FGDs coupled with IDIs carried out with same participants as FGD.

#### Study population and sampling

Participants of the qualitative study are recruited from households where both partners are involved in the intervention: women participating in VSLA and their partner participating in a male reflection group. Women and men in qualitative are recruited in the same villages but are not part of the quantitative study. We plan to conduct 20–30 in depth interviews with women and men or until saturation is reached [58]. Different themes such as gender norms, roles and justice in society, communication between husband and wives, and gendered responsibility in health and in households’ economics will be explored. Observations of women in VSLAs and at their home during the visits will be done throughout the process. Attitudes, the ability to feel confident to speak about anything related to women’s health and the nutrition of children with special regards on the involvement of men will be collected.

